#### Eligibility check

Participants have their eligibility checked and confirmed within the 14 days prior to surgery. Eligibility is confirmed by one of the three operating cardiac surgeons who are clinical investigators for this trial.

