#### Secondary outcomes

Secondary outcomes are:The proportion of patients who receive a RBC transfusion during the intra-operative period and the entire post-operative hospital stayThe mean number of RBC units transfused during the intra-operative period, post-operative period (within the 7 days following AVR surgery) and the entire post-operative hospital stayThe proportion of patients receiving blood product transfusions during the intra-operative period, within the 7 days following AVR surgery and during the entire hospital stayThe mean number of blood product transfusions received during the intra-operative period, within the 7 days following AVR surgery and during the entire hospital stayMean post-operative blood loss (millilitres) measured from chest drains at 6 and 12 hours, and at the time of drain removal, following AVR surgeryOperative success as defined by transthoracic echocardiographic assessment of left ventricular function, and degree of aortic regurgitation, within 6 weeks of AVR surgeryMean post-operative changes in haemoglobin (Hb) within the index hospital stayMean post-operative changes in inflammatory markers on admission to CICU and on day 1 following AVR surgeryProportion of patients reporting moderate or severe post-operative sternal wound pain, measured daily using an 11-point numerical rating scale developed by the trial team, until patient is fit for hospital discharge, and at 6 and 12 weeks following AVR surgeryRates of re-operation following index AVR surgery until 12 weeksRate of conversion to conventional AVR during index surgeryChanges in forced expiratory volume and forced vital capacity on days 3 and 4 and at 6 weeks following AVR surgeryEuroQoL EQ-5D-3L [21] scores, captured at baseline and on day 2, and 6 weeks and 12 weeks following AVR surgery, will be converted to health status scores using the value set (time trade-off) [22] and provide patient-level quality-adjusted life year (QALY) estimates as a health outcome [23]. The EQ-5D-3L is a validated, self-reported outcome measure consisting of five dimensions: mobility, self-care, usual activity, pain/discomfort, anxiety/depression. Each dimension has three levels of response.Mean time at which patients are fit for discharge from hospital following AVR surgeryHealth care utilisation during hospital stay and following discharge to 12 weeks, from medical note review, GP records and patient reportsCost and cost effectiveness estimated from QALY estimates and health care utilisation valued using national reference costs to 12 weeksRates of related adverse events during the 12 weeks following surgery including severity.

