### Sample size calculation

This trial will determine if manubrium-limited ministernotomy is an appropriate clinical alternative to the existing operation (conventional sternotomy) in terms of RBC transfusion requirements in the 7 days following index surgery. Currently, there is clinical and policy equipoise with no intention to extend the use of the new procedure until high-quality randomised controlled trial evidence is available.

Using Fisher’s exact test, 90% power, 5% alpha, 260 patients are required to detect a 17% reduction in the proportion of patients requiring RBC transfusion (13% compared with 30%), using a two-sided test. Recruitment will continue until the target sample size is reached and 260 patients are contributing to the primary outcome.

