#### Measures taken to avoid bias

This trial incorporates a number of methods to avoid bias:Concealment of allocation will be achieved through a web-based randomisation system, described above, managed by DCTU. Named clinical research team members enter a minimum data set per patient before individual allocation to type of sternotomy is provided.Three consultant cardiothoracic surgeons perform all operations as part of this trial. Each is expert in both techniques and does not delegate to other trainee or consultant surgeons.Criteria for blood and blood product transfusions are detailed in the protocol and followed for all patients. Clinical staff members in all cardiothoracic wards follow this protocol. Where clinical need requires blood to be given outside of the protocol, this is documented and described. The trigger for all transfusions is recorded.Patients are blind to the sternotomy procedure, both planned and received, for 2 days following their index surgery. All have an opaque dressing applied to both the sternum and the groin to facilitate blinding; these are only removed, and the patient informed, following their day 2 trial assessments unless clinical need requires earlier removal. Sternal wound pain is assessed using an 11-point numerical rating scale, with all analgesic medication taken in the preceding 4 hours recorded.Fitness for discharge is measured using defined physiotherapy and clinical criteria; these are assessed daily from day 3 by a research team physiotherapist and by the surgical research team. The date that both physiotherapy and clinical criteria are met is defined as the date the patient is fit for discharge. The date of actual discharge is also recorded.Where patients choose to withdraw from the study prior to 7 days following their index surgery, permission is sought to continue data collection to support analysis of the primary endpoint.

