### Governance

The trial is overseen by a TSC, which includes an independent chair and two other independent members (one of whom is a patient). In addition, the trial has a DMC, which meets 6 monthly, and oversees all ethical and safety issues in accordance with a study-specific DAMOCLES charter [30] for DMCs. All members are independent of the study team, although the Trial Manager, Chief Investigator and some other members of the Trial Management Group (TMG) attend the open sessions in order to inform the DMC of trial progress.

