### Reporting of adverse events

AEs and serious adverse events (SAEs) are recorded and reported from the time of index surgery until completion or withdrawal. SAEs are reported within 24 h of the research team becoming aware of the event to the Sponsor. Where required, these events undergo expedited reporting to the Research Ethics Committee. All AEs are assessed for severity, causality, expectedness and seriousness by an Investigator; all are reviewed by the DMC.

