## Discussion

This is the first trial to examine aortic valve replacement via manubrium-limited ministernotomy versus conventional sternotomy when comparing red blood cell transfusion rates following surgery. MAVRIC will determine if manubrium-limited ministernotomy should be adopted as best practice for patients requiring AVR surgery.

It was not possible to blind clinicians to the surgical procedure provided, although transfusion decisions are protocol-driven and should not be procedure-related. The inclusion of patient blinding was in response to a funding panel recommendation. It has been possible to implement this through the use of opaque dressing, which means that patient-reported pain scores at 2 days will be blinded. We will assess the effectiveness of blinding by inviting patients to indicate which treatment they think they have received before removing the dressings.

Surgical trials present significant challenges. The strengths of this trial include a rigorous research design, standardised surgery performed by experienced consultant cardiothoracic surgeons, an agreed anaesthetic regimen, patient blinding and consultant-led patient recruitment. Each discipline within the Cardiothoracic Division at JCUH is supporting and collaborating with the Chief Investigator. MAVRIC will demonstrate that complex surgical trials can be delivered to exemplary standards and provide the community with the knowledge required to inform future care for patients requiring aortic valve replacement surgery.

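### The only listed adverse event outcome is restricted to events judged related by investigators in a trial without clinician blinding, so that comparison is open to differential attribution

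*Protocol article*

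**What the plan says.** All references are to the protocol article.

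- **Secondary outcomes.** The last item is rates "of related adverse events during the 12 weeks following surgery including severity". No outcome in the list counts adverse events, serious adverse events or deaths from all causes. The Abstract names adverse events without the word *related*; the outcomes list is the narrower statement.
- **Reporting of adverse events.** Collection is not restricted by relatedness: "AEs and serious adverse events (SAEs) are recorded and reported from the time of index surgery until completion or withdrawal". Causality is then judged: "All AEs are assessed for severity, causality, expectedness and seriousness by an Investigator; all are reviewed by the DMC".
- **Discussion.** On blinding of staff: "It was not possible to blind clinicians to the surgical procedure provided".
- **Eligibility check** and **Measures taken to avoid bias.** Eligibility is confirmed by "one of the three operating cardiac surgeons who are clinical investigators for this trial", and "Three consultant cardiothoracic surgeons perform all operations as part of this trial".
- **Governance.** Of the data monitoring committee (DMC): "All members are independent of the study team".

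The article describes no blinded or independent assessment of causality.

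**The concern.** In a randomised comparison, background events are expected equally in both arms, so they need not be removed one by one. Removing them on a judgement made without blinding gives up part of that protection. If investigators are readier to call an event related in one arm, the outcome shows a difference that is not there or hides one that is.

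The article itself gives reasons why attribution might differ by arm. Femoral venous cannulation belongs to the intervention only (Interventions), so a groin event points to the arm. The Inflammatory markers section says that bypass and cross-clamp times are longer in minimally invasive surgery. It also raises a larger inflammatory response to sternotomy as a possible mechanism, and links such a response to atrial fibrillation and kidney injury. The same kidney injury could be attributed to surgery in either arm, depending on which mechanism the assessor favours.

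At stake is the harm side of the trial's conclusion. The Discussion says the trial will settle whether the technique should become best practice. A death or stroke judged unrelated would not count in the one adverse event comparison listed.

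**Working it through.** **The plan's own figure.** The article has one design calculation: "90% power, 5% alpha, 260 patients are required to detect a 17% reduction" (30% versus 13%, two-sided, Fisher's exact test). Full enumeration of the Fisher test at 130 per arm gives power 0.902, so it reproduces. This point does not depend on it; 130 per arm (260 / 2, 1:1 allocation) is used below only as a realistic size.

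**Which events count.** Setting the sections side by side:

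1. Recorded: all AEs and SAEs (Reporting of adverse events).
2. Compared under the listed AE outcome: the related ones (Secondary outcomes).
3. The step from 1 to 2 is an investigator's causality judgement, with no blinding stated.

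**What the filter can do.** Let p be the true proportion of patients with an AE, and r the share of events called related. With one event per affected patient, the reported proportion is p × r. If p is the same in both arms, the apparent risk ratio is (p × r₁) / (p × r₀) = r₁ / r₀, whatever p is. Every p and r below is an assumption; the documents give none.

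- *Spurious difference:* p = 40% in both arms, r = 65% (intervention) and 50% (control). 0.40 × 0.65 = 26%; 0.40 × 0.50 = 20%; ratio 26 / 20 = 1.30. With the shares swapped, 20 / 26 = 0.77.
- *Hidden difference:* true risks 52% and 40% (ratio 1.30), r = 50% and 65%. 0.52 × 0.50 = 26%; 0.40 × 0.65 = 26%; ratio 1.00.
- *Two events per affected patient, labelled independently:* the chance of at least one related event is 1 − (1 − r)². For r = 65% this is 1 − 0.35² = 0.8775; for r = 50% it is 1 − 0.50² = 0.75. With p = 40% the reported proportions are 35.1% and 30.0%, ratio 1.17. The size therefore depends on the one-event assumption.

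**Chance of a falsely significant result.** Equal true risk, 130 per arm, one event per affected patient, Fisher test at two-sided 5%, by full enumeration:

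| Share called related | Apparent ratio | True risk 20% | True risk 40% | True risk 60% |
|---|---|---|---|---|
| 50% vs 50% | 1.00 | 3.0% | 3.5% | 3.7% |
| 50% vs 40% | 1.25 | 5.5% | 10.3% | 15.7% |
| 60% vs 40% | 1.50 | 13.7% | 31.2% | 51.1% |

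The table shows what differential attribution could do. It does not estimate what will happen in this trial.

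**The case against.** **Safety is not compared only through this outcome.** A reader might infer that it is. The documents do not support that: re-operation to 12 weeks, conversion, drain blood loss and echocardiographic success are separate secondary outcomes with no causality step. Conversion in particular is counted in its own right, so attribution cannot distort it. This stands, and it confines the point to the adverse event outcome.

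**The operating surgeon is not named as the assessor.** A reader might infer that surgeons judge events in their own patients. The text says only that an investigator does so; the surgeons are called investigators in connection with eligibility. They may be among the assessors, and no more can be said. The lack of clinician blinding is stated outright.

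**Related to what?** The article does not define the term. If it means related to valve replacement, which both arms undergo, labelling could be much the same in both. This is fair, and it means differential labelling is a possibility and not a finding. The definition may stand in the full protocol, which is not shown. Deaths and serious events judged unrelated would still be left out.

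**The DMC sees every event.** True, and its members are independent. Its review is oversight, however; it is not described as blinded adjudication and does not change which events the outcome counts.

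**The numbers are assumed.** Also true. Even the 20% versus 26% example would not be significant at 130 per arm: pooled proportion 0.23, standard error √(2 × 0.23 × 0.77 / 130) = 0.052, z = 0.06 / 0.052 ≈ 1.15, p ≈ 0.25. A biased estimate matters in a safety comparison whether or not it is significant, but no size can be claimed. Removing clearly unrelated events also reduces noise; that is a real benefit, though a small one if the judgement behind it is not blinded.

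**Conclusion.** The point holds for the adverse event outcome and only for it. As written, that outcome filters a randomised comparison through a causality judgement for which no blinding is described, in a trial where clinicians knew the procedure. It is open to bias in either direction and can omit serious events, including deaths. The documents do not show that attribution will differ, or that any bias would favour a particular arm. The article also does not say that an all-cause table will be withheld; one may be planned elsewhere, but the listed outcome does not call for it.

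The size cannot be estimated from the documents. On the assumed values, equal true risks appear as 20% versus 26% (ratio 1.30, or 0.77 with the labels reversed). The primary outcome, its analysis and the sample size are untouched. The change is worth making because it replaces a weaker comparison with a better one at almost no cost.

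**What to change.** In Secondary outcomes, and in the analysis plan to match, make the between-arm adverse event outcome the proportion of patients with any AE, and the proportion with any SAE, from all causes and including death, within the 12 weeks following surgery already stated, by severity. Report the related subset by arm as descriptive only.

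The cost is one amended outcome line and a little extra tabulation. No new data collection is needed, because all AEs and SAEs are already recorded from index surgery to completion or withdrawal. No sample size or power figure changes. One limit should be stated with the results: under Retention of participants, follow-up after withdrawal continues only where the withdrawal was due to a related adverse event, so the number of patients withdrawn before 12 weeks should be shown by arm.

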
### Participant timeline

Patients are followed for 12 weeks, with follow-up at 6 weeks and 12 weeks after discharge from hospital following their index AVR operation. Figure 3 provides a flow chart of the patient pathway in the MAVRIC trial.

**Fig. 3 Fig3:**
[figure not shown]
Flow chart of the patient pathway for the MAVRIC trial

### Sample size calculation

This trial will determine if manubrium-limited ministernotomy is an appropriate clinical alternative to the existing operation (conventional sternotomy) in terms of RBC transfusion requirements in the 7 days following index surgery. Currently, there is clinical and policy equipoise with no intention to extend the use of the new procedure until high-quality randomised controlled trial evidence is available.

Using Fisher’s exact test, 90% power, 5% alpha, 260 patients are required to detect a 17% reduction in the proportion of patients requiring RBC transfusion (13% compared with 30%), using a two-sided test. Recruitment will continue until the target sample size is reached and 260 patients are contributing to the primary outcome.

### Recruitment

Patients undergoing isolated AVR surgery will be identified at the point of referral or from the inpatient waiting list by the clinical team, and will be approached by a member of the research team about participation in MAVRIC. Patients will be consented by a Consultant Cardiothoracic Surgeon or a Surgical Registrar.

### Allocation

Following consent, eligible patients are randomised to receive AVR by manubrium-limited ministernotomy or by conventional sternotomy following confirmation of eligibility. Randomisation is made using a permuted block randomisation, stratified by logistic EuroSCORE [24] (low risk 0–3.50%, moderate risk 3.51–7.5% and high risk >7.5%) and by pre-operative Hb (90–125 g/L, 126–140 g/L, >140 g/L). A web-based randomisation system, managed by Durham Clinical Trials Unit (DCTU), will ensure concealment of allocation.

### Blinding

This is a single-blind trial. Patients are not informed of the type of sternotomy they are planned to receive, or do receive, until completion of the pain assessment on day 2 following their operation. To enable blinding post-operatively, all patients have a trial-specific opaque dressing applied to their sternal wound and to their groin.

#### Measures taken to avoid bias

This trial incorporates a number of methods to avoid bias:Concealment of allocation will be achieved through a web-based randomisation system, described above, managed by DCTU. Named clinical research team members enter a minimum data set per patient before individual allocation to type of sternotomy is provided.Three consultant cardiothoracic surgeons perform all operations as part of this trial. Each is expert in both techniques and does not delegate to other trainee or consultant surgeons.Criteria for blood and blood product transfusions are detailed in the protocol and followed for all patients. Clinical staff members in all cardiothoracic wards follow this protocol. Where clinical need requires blood to be given outside of the protocol, this is documented and described. The trigger for all transfusions is recorded.Patients are blind to the sternotomy procedure, both planned and received, for 2 days following their index surgery. All have an opaque dressing applied to both the sternum and the groin to facilitate blinding; these are only removed, and the patient informed, following their day 2 trial assessments unless clinical need requires earlier removal. Sternal wound pain is assessed using an 11-point numerical rating scale, with all analgesic medication taken in the preceding 4 hours recorded.Fitness for discharge is measured using defined physiotherapy and clinical criteria; these are assessed daily from day 3 by a research team physiotherapist and by the surgical research team. The date that both physiotherapy and clinical criteria are met is defined as the date the patient is fit for discharge. The date of actual discharge is also recorded.Where patients choose to withdraw from the study prior to 7 days following their index surgery, permission is sought to continue data collection to support analysis of the primary endpoint.

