### Outcomes

#### Primary outcome

The primary outcome is the proportion of patients who receive a RBC transfusion post-operatively and within 7 days of AVR surgery.

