### Retention of participants

Patients who withdraw have all data collected up until the point of withdrawal included in the study except where withdrawal is due to a related adverse event (AE), in which case the patient is followed until a stable outcome is achieved.

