### Statistical methods

The null hypothesis is that there will be no difference in the proportion of patients receiving RBC transfusion after manubrium-limited ministernotomy when compared to conventional sternotomy for AVR.

This trial will determine if manubrium-limited ministernotomy is an appropriate clinical alternative to the existing operation (conventional sternotomy) in terms of RBC transfusion requirements in the 7 days following index surgery. An analysis of the primary endpoint will be conducted using Fisher’s exact test. A sensitivity analysis will also be performed for the primary endpoint using a logistic regression model to account for potential confounders and stratification factors. Continuous outcomes will be analysed using general linear models. Correlation between repeated measures per patient will be appropriately accounted for in the linear models where applicable. Binary data will be analysed using logistic regression where there are no repeated data per patient. Repeated binary data will be analysed using generalised estimating equations. Stratification factors and chance baseline imbalances following randomisation will be explored for the primary and secondary outcomes.

Analysis will follow intention-to-treat principles with patients analysed according to the surgery allocated by randomisation and irrespective of surgery received, subsequent management or events [26]. Every effort will be made to retain and include all patients who receive surgery as part of the trial.

A prospective economic evaluation is integrated into the trial design and applies an NHS perspective to the inclusion of costs. Mechanisms of missingness within the data will be explored, and multiple imputation methods will be applied to impute missing data and minimise bias. Imputation sets will be used in bivariate analysis of costs and QALYS to generate incremental cost per QALY estimates and credible intervals [27–29]. It is anticipated that incremental costs and benefits will be captured within the trial, although extrapolated economic modelling will be considered if appropriate. Findings will be presented on the incremental cost-effectiveness ratio (ICER) plane and using cost-effectiveness acceptability curves (CEACs).

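### Collection after withdrawal is limited to the 7-day primary endpoint and related adverse events, so record-based 12-week secondary outcomes of withdrawn patients would be missing

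*Protocol article*

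**What the plan says.** Three sections of the protocol article govern data after withdrawal.

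- **Measures taken to avoid bias:** "Where patients choose to withdraw from the study prior to 7 days following their index surgery, permission is sought to continue data collection". The stated aim is limited: "permission is sought to continue data collection to support analysis of the primary endpoint".
- **Retention of participants:** "Patients who withdraw have all data collected up until the point of withdrawal included in the study", with one exception: "except where withdrawal is due to a related adverse event (AE), in which case the patient is followed until a stable outcome is achieved".
- **Reporting of adverse events:** adverse events and serious adverse events are "recorded and reported from the time of index surgery until completion or withdrawal".

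The primary outcome is "the proportion of patients who receive a RBC transfusion post-operatively and within 7 days of AVR surgery". Secondary outcomes run longer. Re-operation, related adverse events, health care utilisation and cost are all taken to 12 weeks, and utilisation is drawn from medical notes, GP records and patient reports. Under Blinding, patients are not told their operation "until completion of the pain assessment on day 2 following their operation". Statistical methods commits to intention to treat and adds: "Every effort will be made to retain and include all patients who receive surgery as part of the trial".

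**The concern.** The stated permission rule has a time limit (withdrawal before day 7) and a purpose limit (the primary endpoint). Someone who withdraws on day 10 because visits are a burden falls outside it, and collection then ends, even for outcomes that need no further contact with the patient.

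Patients know their operation for nearly all of the 12-week period, and the Discussion accepts that clinicians cannot be blinded. Withdrawal could therefore be related to the arm or to the patient's course. Longer follow-up also depends on an unblinded judgement that the reason for leaving was a related adverse event. At stake are the 12-week comparisons of re-operation, adverse events and resource use. Data that could have been requested would be missing, possibly informatively.

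**Working it through.** **1. What the text provides in each case**

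| Withdrawal | Collection afterwards |
|---|---|
| Before day 7, permission given | Transfusion data for the 7-day endpoint; nothing stated to 12 weeks |
| Before day 7, permission refused | None |
| Day 7 or later, not for a related adverse event | None; adverse event recording stops |
| Any time, because of a related adverse event | Follow-up until stable; no mention of re-operation or resource use to 12 weeks |

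The sections also fit together loosely. Retention of participants names one exception and does not mention the day 7 permission route. Reporting of adverse events stops at withdrawal without mentioning the exception for related events.

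**2. What records could supply (Secondary outcomes)**

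- Health care utilisation: two of the three named sources (medical notes and GP records) need no patient contact. Cost follows from utilisation.
- Re-operation and related adverse events: no source is named. In a single-Trust trial hospital notes are a likely source, but that is an inference.
- QALYs: these need the patient-completed EQ-5D-3L, so records cannot replace them.

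**3. Share of the window that is unblinded**

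Twelve weeks from surgery is 12 × 7 = 84 days.

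- After day 2: (84 − 2)/84 = 82/84 = 97.6%.
- After day 7, outside the permission rule: (84 − 7)/84 = 77/84 = 91.7%.

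These are shares of time, not of withdrawals. Early withdrawal may be more common than late.

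**4. The plan's own figure**

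Sample size calculation gives 260 patients for 30% against 13%, two-sided 5%, 90% power, Fisher's exact test. By enumeration, exact power is 90.2% at 130 per arm and 89.96% at 129 per arm, so 2 × 130 = 260 reproduces. The Abstract's 270 randomised leaves room for (270 − 260)/270 = 3.7% loss. That allowance concerns the primary outcome. No withdrawal rate to 12 weeks is given.

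**5. Re-operations at risk of being missed**

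Inputs: N = 260; assumed withdrawal w = 3%, 5% or 10%; re-operation risk 6% (Blood transfusion following AVR: 2342 of 41,227, which is 5.7% before rounding).

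Withdrawers = 260 × w. Expected re-operations among them = 260 × w × 0.06.

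| w | Withdrawers | Expected re-operations |
|---|---|---|
| 3% | 7.8 (about 8) | 0.47 |
| 5% | 13 | 0.78 |
| 10% | 26 | 1.56 |

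In the whole trial, 260 × 0.06 = 15.6 would be expected. The middle table rows are maxima given the 6%, as is every row, because they place all of each withdrawer's risk after withdrawal. Two cautions apply: the 6% covers second operations for bleeding only, and withdrawers are taken to have average risk.

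**The case against.** The strongest objection is that this is a condensed article. It refers to an approved version 5 of the protocol, which is not shown, and graded withdrawal options usually sit there or on the withdrawal and consent forms. The article does not say that permission is never sought later. Protecting the primary endpoint and otherwise respecting a patient's wish to leave is a defensible choice. This stands in part: the full protocol may already provide more. But the article is not silent. It states a rule with two limits and lists it as a safeguard against bias, and as stated the rule is too narrow for the 12-week outcomes and for the promise of every effort to include operated patients.

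A second objection is that the plan already copes. Missingness will be explored and multiple imputation applied, and the adverse event outcome counts related events, which the Retention exception covers. The imputation is described only within the economic evaluation, and it is weaker than data that could be obtained. The exception covers patients who leave because of a related event, not those who leave for another reason and have one later.

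Stronger readings are tempting, but the document does not support them:

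- A reader might infer that two or three lost re-operations would materially change the comparison. Even at 10% withdrawal the expected number is below 2, and nothing suggests that the events would all fall in one arm.
- A reader might infer that learning the allocation makes patients withdraw. The document says only when they are told.
- A reader might infer that the 12-week outcomes are lost in general. Only patients who withdraw are concerned.

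**Conclusion.** The point holds as a limitation of secondary outcomes. Followed as written, the rules leave re-operation, adverse events and the record-based part of health care use and cost missing after withdrawal, outside the follow-up of related adverse events. Because most of the window is unblinded, the loss could be informative; whether it would be is unknown.

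The effect is probably small: at most about 0.5 to 1.6 re-operations among 8 to 26 withdrawers. This rests on assumed withdrawal of 3% to 10%, on a national 6% figure for bleeding with no stated time window, and on average risk among withdrawers. The number of patients actually affected cannot be derived from the document. The primary endpoint and the sample size of 260 are unaffected, and EQ-5D-based QALYs would not be recovered by the change. It is worth making because it is cheap, not because the trial's main conclusion depends on it.

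**What to change.** At any withdrawal, whenever it occurs and for whatever reason, offer the patient the option to stop visits and questionnaires only. Ask permission to keep collecting transfusion, re-operation, adverse event, death and health care use data from hospital and GP records to 12 weeks. Then align Measures taken to avoid bias, Retention of participants and Reporting of adverse events, so that all three state the same rule and its exceptions. If the full protocol already contains such an option, only the alignment is needed.

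The cost is a change to the withdrawal form and consent wording; review of notes and GP records is already planned for utilisation. Some patients will decline, and their data then stop as now. Recruitment began in March 2014, so the change helps only patients whose 12-week follow-up is still open.
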